### Research Design

Our study uses a mixed methods design and is being conducted in eight European countries: France, Ireland, Italy, Poland, Portugal, the Netherlands, Spain, and Sweden. Our design is correlational and not randomized. We will recruit participants who are already engaged with either Housing First or traditional services and collect quantitative data via questionnaires at two time points: baseline (T0) and follow-up (T1). This will allow us to control for baseline nonequivalence on demographic characteristics and other individual differences, such as lifetime homelessness, length of time in current accommodation, alcohol and substance use, education, and physical health. A subset of participants from each country who completed the questionnaires will complete an in-depth, qualitative, capabilities interview. In this paper, we describe the core procedures and methods that will be completed across all eight study sites.

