##### Questionnaire Administration

Research interviewers will meet individually in a quiet location chosen by participants. After a short ice-breaker conversation intended to build rapport, the researcher will explain the study and obtain informed consent before administering the questionnaire. The 13 measures included in the baseline questionnaire are presented in Table 1. Research interviewers will read each item to participants using a standardized procedure and record participants’ responses on the questionnaires. When the questionnaire is complete, the researcher will ask permission to contact the person to complete the questionnaire 6 months later.

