#### Statistical Analysis

We plan to compare participants who are engaged in Housing First programs to participants engaged in traditional services to determine whether they differ on service and support features, rehabilitation-related recovery outcomes, and growth-related recovery outcomes at baseline and at follow-up. Based on previous experience [60] in which participants chose to skip items and even entire measures, we expect to have missing data on most measures. We also expect attrition at T1 because participants have died, cannot be located, or do not wish to complete the questionnaire a second time. We will use Little’s *missing completely at random* test to determine whether data is *missing completely at random*, *missing at random*, or *neither*. We will manage data that is *missing completely at random* or *missing at random* using one of two approaches, depending on the research question, statistical technique, and software package. In the first technique, we will use expected maximization imputation techniques [61]. We will employ this technique with cross-sectional analyses of variance and multiple regression with SPSS, version 24.0 (IBM Corp). In the second technique, we will employ maximum likelihood in multi-level modelling with Mplus, version 8.2 (Muthén & Muthén) [62].

We will use T0 data to control for differences at baseline while examining patterns of association at T1. As individual data will be nested within program data, we will use multi-level modelling to account for Level 1 and Level 2 differences in intercepts, slopes, and intercept-slope covariances while controlling for baseline scores, country of residence, and demographic factors. If there are significant differences in the intercepts or slopes for recovery outcomes, we will determine whether these differences are accounted for by program membership—Housing First versus traditional services—and setting features.

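### The clustered, baseline-adjusted test of programme type and setting features is made conditional on a prior significant result, in conflict with the abstract and objective 3, and its individual-level slope terms do not suit a two-wave design

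*Protocol article*

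**What the plan says.** All places are in the protocol article.

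- **Statistical Analysis, the gate.** "If there are significant differences in the intercepts or slopes for recovery outcomes, we will determine whether these differences are accounted for" by programme type and setting features. Both explanatory steps for recovery outcomes stand behind this condition.
- **Statistical Analysis, the model.** The reason given for a multilevel model is clustering: "As individual data will be nested within program data". The model is to "account for Level 1 and Level 2 differences in intercepts, slopes, and intercept-slope covariances while controlling for baseline scores", country and demographic factors. The word slope is not defined.
- **Statistical Analysis, the role of T0.** "We will use T0 data to control for differences at baseline while examining patterns of association at T1".
- **Statistical Analysis, opening.** The two service types are to be compared on setting features and on both groups of recovery outcomes, at baseline and follow-up, with no condition. Cross-sectional analysis of variance and multiple regression are named alongside multilevel modelling.
- **Abstract, Methods.** Multilevel modelling will test the difference between Housing First and traditional services on the key outcomes. No condition is attached.
- **Objectives, third specific objective.** Whether setting features predict T1 recovery outcomes, given T0 scores, is to be determined. No condition is attached.
- **Research Design and Questionnaire Administration.** The design is not randomised. There are two waves, T0 and T1, six months apart.

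**The concern.** The abstract and objective 3 promise tests that the Statistical Analysis section performs only after a preliminary significant result. Both cannot be followed.

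The gate also asks a different question from the one of interest. Whether programmes vary at all is a diffuse question with many degrees of freedom. Whether Housing First differs from traditional services is a single directed contrast, and it can be clear when the diffuse test is not. In a non-randomised study with participants clustered in programmes, the gated analysis is the one that adjusts for T0 and respects clustering. If the gate stays shut, what remains is named only as cross-sectional analysis of variance and regression, and objective 3 has no stated analysis for recovery outcomes.

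The gate also partly refers to slopes. With two waves, a slope at the level of the individual may be inestimable or may not exist, depending on what is meant.

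**Working it through.** **1. The article's own figures.** Baseline target: 8 × (38 + 45) = 664, as stated. T1 target: 240 + 240 = 480, so implied retention is 240/304 = 78.9% in Housing First and 240/360 = 66.7% in traditional services. The article gives no alpha, power, effect size, ICC or number of programmes, so there is no power figure to reproduce.

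**2. Can individual slopes be estimated?** Suppose T0 and T1 are both outcomes and time is coded 0 and 1. Let the individual-level parameters be intercept variance a, intercept-slope covariance c, slope variance b and residual variance s. Then:

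- Var(T0) = a + s
- Var(T1) = a + 2c + b + s
- Cov(T0, T1) = a + c

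Three moments must determine four parameters. Two different sets give identical data:

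- (a, c, b, s) = (0.5, 0, 0.3, 0.5): variances 1.0 and 1.3, covariance 0.5
- (a, c, b, s) = (0.6, −0.1, 0.5, 0.4): variances 1.0 and 1.3, covariance 0.5

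The Jacobian rank is 3 of 4. Adding a programme level gives rank 6 of 7; the programme-level block on its own is identified (3 of 3). If T0 is instead a covariate, each person has one outcome record and no individual time slope exists. A T1-on-T0 slope that varies by programme is identified (4 of 4).

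**3. What does the gate cost?** Assumptions, none from the article: K programmes of equal size (16, 32 or 48), balanced over eight countries and two types; residual ICC of 0, 0.02 or 0.05; a true type difference of 0.3 SD of the outcome as analysed; 5% tests. Only the total of 480 comes from the article.

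- Gate: F = between-programme mean square within country / within-programme mean square, on K − 8 and 480 − K degrees of freedom.
- Direct test: t = difference in programme means / √(4s²/K), where s² is now the residual variance of programme means, with country adjusted, on K − 9 degrees of freedom.
- Gated power: the share of runs in which both are significant.

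At ICC 0 the type difference gives both tests the same noncentrality, 480 × 0.15² = 10.8. The direct test spends it on one degree of freedom; the gate spreads it over 8, 24 or 40.

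Results from 40,000 runs per setting:

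| Programmes | ICC | Gate opens | Direct power | Gated power | Significant direct results discarded |
|---|---|---|---|---|---|
| 16 | 0 | 62% | 80% | 54% | 33% |
| 16 | 0.02 | 77% | 62% | 52% | 16% |
| 16 | 0.05 | 88% | 44% | 41% | 7% |
| 32 | 0 | 39% | 88% | 36% | 59% |
| 32 | 0.02 | 65% | 80% | 55% | 30% |
| 32 | 0.05 | 88% | 68% | 62% | 9% |
| 48 | 0 | 29% | 89% | 27% | 70% |
| 48 | 0.02 | 54% | 84% | 48% | 43% |
| 48 | 0.05 | 83% | 76% | 65% | 14% |

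Gated power cannot exceed direct power by construction; the question is how far it falls. The fall is largest when programmes of the same type behave alike.

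If the gate were a two-sided 5% Wald test of the programme variance, at 0.3 SD it would open in 0% of runs with 16 programmes, 3% to 44% with 32, and 5% to 48% with 48.

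**The case against.** A reader might infer that programme type is examined only if the gate opens, so that the study's main contrast could vanish. The article does not support that. The Statistical Analysis section opens with an ungated comparison at both time points and names analysis of variance and regression, and the abstract states the multilevel test outright. This objection stands. What the gate puts at risk is the clustered, T0-adjusted contrast and the setting-feature step.

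A reader might also infer that the planned model as a whole cannot be estimated. That too goes beyond the text. Slope is undefined; a programme-level time slope or a T1-on-T0 slope varying by programme is estimable, and the intercept route through the gate stays open. The two criticisms of the individual slope apply to different models, T0 as outcome or T0 as covariate, and only one can be in use. But the estimable alternatives sit at the programme level, so they do not rescue the Level 1 slope and covariance that the text names.

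The size of the loss is open to challenge. The article speaks of significant differences and names no variance test; the F test is one reading. The simulated gate covers intercepts only, although slopes could also open it. The steepest falls need a residual ICC of 0, and at ICC 0.05 the loss is 3 to 11 percentage points. All of this stands, and it limits the figures to illustrations.

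Finally, an article may leave full model specification to an analysis plan. That would excuse silence, but the condition is a stated rule and it conflicts with other statements in the same article.

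**Conclusion.** The point holds in limited form. The Statistical Analysis section makes the multilevel, baseline-adjusted examination of programme type and setting features on recovery outcomes conditional, whereas the abstract and objective 3 do not. The ungated analyses are no full substitute, because none of them is stated to handle both clustering and T0 scores.

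Under an omnibus F gate at 0.3 SD, the loss of power runs from 3 percentage points (16 programmes, ICC 0.05) to 62 (48 programmes, ICC 0). Its direction is certain; its size depends on programme numbers, ICC, effect size and a gate test that the article does not give.

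The slope defect is narrower. Individual time slopes with a free residual variance are not identified from two waves, and are absent if T0 is a covariate.

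**What to change.** - Delete the significance condition.
- For each recovery outcome, fit T1 on the T0 score, country and the planned covariates, with a random programme intercept. Enter programme type as a fixed effect in every case, and report its estimate and 95% CI whatever any test of variation shows.
- Fit the setting-feature models for objective 3 without condition as well, since the same sentence gates them.
- Drop the individual-level slope and intercept-slope covariance terms. If a slope is wanted, define it as the T1-on-T0 regression varying across programmes, as a secondary check.

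The cost is a change of analysis wording. No further data are needed, the model becomes simpler, and the section then agrees with the abstract and objective 3.

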### Qualitative Methods and Analysis

#### Participants

From the full sample of participants who complete the quantitative questionnaire at T1, we will invite 10 participants in each country (Housing First, n=5, and traditional services, n=5) to complete a semistructured interview focused on the 10 domains of capabilities identified by Nussbaum [42]. Partners will select participants with an aim for gender and age balance, where possible. Given the demands of a qualitative interview, HOME_EU Consortium partners will be asked to select participants who, from their previous research encounters, seemed capable of engaging with questions and enjoyed talking but also those who were able to focus and effectively articulate their thoughts.

Partners will only recruit participants to the qualitative study if they consented to be contacted again about follow-up research. These potential participants will be invited to participate in a qualitative interview about their experiences of homeless services, either over the phone or in person. Participants will be told that the interview will take about 1 hour and will be audio recorded, their data will be anonymized, and they will receive a €20 shopping voucher in return for participation. If they agree, partners will arrange a time and place to meet the participant.

#### Semistructured Capabilities Interviews

One of the key objectives of *Homelessness as Unfairness* is to explore the capabilities sets [28,42,63] of homeless services users in Europe and to identify the ecological factors that enable or block these capabilities sets (eg, Maton, 2008 [64]). To achieve this objective, our aim for the qualitative interviews is to deeply explore the capabilities sets of 10 homeless services users (Housing First, n=5, and traditional services, n=5) in each country. We developed an interview guide to explore homeless services users’ subjective accounts of their central functioning capabilities [42] (see Table 1 and Greenwood et al, 2013 [27]). In developing this interview guide, we followed Shinn’s [28] suggestions to examine these capabilities sets in terms of participants’ behaviors or activities that a person freely chooses to do or not to do. We also aim to explore their subjective understanding of internal and external affordances and constraints, which are intrapersonal factors and environmental factors that the person perceives to either facilitate or restrict the range of their realistically possible capabilities.

#### Sampling and Recruitment

##### Participant Selection

A total of 5 Housing First services-engaged participants and 5 traditional services-engaged participants who complete the T1 quantitative questionnaire will be recruited in each country to complete the qualitative interview. When choosing and recruiting these participants, we will aim for gender balance, where possible, and aim to have a range of ages represented in the sample. Because the capabilities interview addresses many abstract concepts, such as freedom and rights, ideal candidates for the qualitative interviews are participants who engaged well with the quantitative questionnaire, who are reflective on their lives, and are able to focus their attention and compellingly describe their experiences. Because we do not want the experience of completing the capabilities interview to influence participants’ responses on the quantitative measures, the T1 questionnaire will be completed prior to the interview.

##### Procedures

Interviews will be prearranged to occur at a quiet location chosen by the participant. Research interviewers should greet the participant and have a short ice-breaker chat, then explain the purpose of the interview and give an indication of how long the interview will last. After obtaining informed consent, the interviewer will begin the interview. With the participant’s consent, the interview will be digitally recorded.

Researchers will follow the semistructured interview guide (available upon request from the first author) in a way that adapts to each participant’s responses. The interview guide is structured so that the interviewer can take the interviewee through a discussion of the domains of capabilities identified by Nussbaum [42]. The prompts for each of the domains are constructed so that the interviewer can gain insight not only into the types of choices that are made in these areas, but also the breadth of choices and the affordances and constraints on choices in each domain. The main purpose is to understand the “range of realistic possibilities” [28], that is, the capabilities set that is available to each interviewee, along with the forces they experience as either facilitating or constraining their capabilities.

The interviewers will ask the interviewees to describe themselves in terms of each domain, their range of capabilities in each domain, the things they could do but do not want to do in each domain, the things they cannot do in that domain but would like to, and the factors they experience as blocking or facilitating their capabilities in each domain. Once all the domains have been covered, the interviewer will ask the participant to reflect on the conversation and see if they have anything they would like to add or clarify. Participants will be thanked for their time and provided with a €20 shopping voucher in return for their contribution. They will be invited to contact the research team with any follow-up questions or comments.

#### Qualitative Analyses

Each digitally recorded interview will be transcribed verbatim and anonymized. A deductive coding scheme based on the capabilities domains will be used by all Consortium partners to code each transcript (available upon request from the first author). Two independent coders will code each interview and then meet to agree on the codes. The coded excerpts will then be translated into English using the procedures agreed upon by Consortium partners [58]. The two independent coders will then agree on the English translation of the coded excerpts. The interview codes will be provided to the lead researchers on the Service Users’ Experiences Study, who will collate the codes obtained in each country and enter them into NVivo 11 software (QSR International) for thematic analysis [65].

### Data Synthesis

Qualitative and quantitative data from the Service Users’ Experiences Study component of the HOME_EU study of *Homelessness as Unfairness* will be triangulated with findings from our studies with citizens, policy makers, and service providers. Our aim is to produce a holistic understanding of homelessness across eight European countries that can be used to shape national and European social policy, encourage best practices in homeless services, reverse unfairness and inequality associated with homelessness, and promote recovery and inclusion in civil society.

### Ethics and Data Access

The *Homelessness as Unfairness* project received ethics approval from the lead partners’ (JO and [name]) home university’s research ethics committee (ie, institutional review board). Each of the Consortium partners negotiated ethics approval with their home institutions. For example, the Irish team submitted evidence of approval from the lead partner’s university, along with a description of the work to be carried out with participants in Ireland.

A separate ethics work package was developed to ensure research integrity and protection of participants and researchers. Access to the data will be controlled by each Consortium partner. Completed questionnaires will be anonymized and stored separately from signed informed consent forms. Anonymized data will be input into SPSS, version 24.0 (IBM Corp), files stored on password-protected computers. Data files will be shared electronically via a secure data-sharing program. Access to the data will be limited to core personnel working on the project.

## Results

The study is registered with the European Commission (registration number: H2020-SC6-REVINEQUAL-2016/ GA726997). Two press releases, a research report to the funding body, two peer-reviewed articles, and an e-book chapter are planned for dissemination of the final results. The project was funded from September 2016 through September 2019. Expected results will be disseminated in 2019 and 2020.

## Discussion

We will use the findings from this research to formulate recommendations for European social policy on the configuration of homeless services and the scaling up and scaling out of Housing First programs. From our findings, we will draw conclusions about the setting features that promote individuals’ exits from homelessness, rehabilitation, and recovery.

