Since its first implementation, Housing First has been disseminated across the globe. The first randomized and controlled trial was conducted in New York City, in which Housing First was compared to treatment as usual [21,22]. The largest randomized trial of Housing First thus far was conducted in Canada [23] and a third randomized trial was conducted in France [24]. The positive outcomes of these trials spurred widespread dissemination and nonexperimental pilot and demonstration projects [4,5]. Although the exact number of Housing First programs is unknown, it has been widely disseminated in North America, Europe, Australia, and New Zealand [25,26]. Despite Housing First’s widespread reach and strong evidence base, most European homeless services continue to follow the treatment-first model [27]. Researchers and practitioners continue to work together to expand the evidence base for Housing First through rigorous experimental and observational trials. This study’s comparison of Housing First and traditional services in eight European countries aims to demonstrate not only that Housing First reverses homelessness in these different contexts, but to identify the setting features that explain how it works and, in doing so, produce translational findings that may have widespread influence in policy and practice.

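### The aims and conclusions are worded as causal effects, but the design is a correlational comparison of people already using the services

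*Protocol article*

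**What the plan says.** The protocol article describes the same study in two registers.

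**Design and analysis.** Research Design states "Our design is correlational and not randomized" and "We will recruit participants who are already engaged with either Housing First or traditional services". Statistical Analysis says "We will use T0 data to control for differences at baseline" while looking at associations at T1, using a multi-level model that also adjusts for country and demographics. Research Design adds other measured T0 variables: lifetime homelessness, time in current accommodation, alcohol and substance use, education and physical health. Under Objectives, the third specific objective asks only whether setting features predict T1 outcomes given T0 scores.

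**Aims and conclusions.** In the Background, the comparison "aims to demonstrate not only that Housing First reverses homelessness in these different contexts" but also "to identify the setting features that explain how it works". The Discussion says "we will draw conclusions about the setting features that promote" leaving homelessness, rehabilitation and recovery, and that the findings will be used to "formulate recommendations for European social policy on the configuration of homeless services" and on expanding Housing First. The abstract's Conclusions repeat both Discussion statements. No section qualifies this wording.

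**The concern.** To demonstrate that a programme reverses homelessness, to explain how it works, or to say that a feature promotes recovery is to make a causal or mechanistic claim. These claims are fixed before the data are in, and the design named in the same article does not deliver them by itself.

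Who enters Housing First, and who lives in a setting with a given feature, is decided by programmes and users on grounds that the study need not have measured. The T0 questionnaire comes after that decision, so T0 values may already carry the effect of the service. The stated product is policy advice across Europe, and a reader of that advice would take an adjusted difference as what would happen if services were changed.

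**Working it through.** **1. Passages side by side.**

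| Place | Strength of claim |
|---|---|
| Research Design | correlational, not randomised, current users |
| Objectives, third specific objective | prediction |
| Statistical Analysis | association at T1, adjusted for T0 |
| Background | demonstration and mechanism |
| Discussion; abstract Conclusions | features that promote outcomes; policy recommendations |

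The last two rows go beyond the first three.

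**2. What T0 adjustment can do.** It removes differences in the measured variables as they stand at T0. It does not recover the groups as they were before service entry. Time in current accommodation, substance use and T0 recovery scores may all have been changed by the service. The Background describes Housing First as supplying independent flats, so housing status may be partly settled by group before T0. Adjustment can therefore leave selection bias in place, or remove part of a real effect.

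**3. Sample size as stated.** T0: 8 × (38 + 45) = 304 + 360 = 664, which matches Sample Size and Retention Plan. With 240 per group at T1, the implied attrition is 1 − 240/304 = 21.1% for Housing First and 1 − 240/360 = 33.3% for traditional services. The article states no alpha, power, effect size or SD, so the 240 itself cannot be re-derived.

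**4. Illustration of size.** Input from the article: 240 per group at T1. Assumptions of this review: two-sided 5% test, true effect zero, bias b (in SD units) remaining *after* adjustment, and design effect DE for nesting in programmes.

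- SE = √(2 × DE / 240), which is 0.091 at DE 1 and 0.129 at DE 2
- P(significant) = Φ(b/SE − 1.96) + Φ(−b/SE − 1.96)
- b = 0.10, DE 1: 0.10/0.091 = 1.095, giving Φ(−0.865) + Φ(−3.055) = 0.195
- b = 0.10, DE 2: 0.10/0.129 = 0.775, giving Φ(−1.185) + Φ(−2.735) = 0.121

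| Residual bias (SD) | DE 1 | DE 2 | DE 3 |
|---|---|---|---|
| 0 | 5.0% | 5.0% | 5.0% |
| 0.10 | 19.5% | 12.1% | 9.7% |
| 0.20 | 59.1% | 34.1% | 24.4% |
| 0.30 | 90.8% | 64.2% | 47.5% |

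One way to reach 0.10 SD is an unmeasured trait 20 percentage points more common in one group and worth 0.5 SD on the outcome: 0.20 × 0.5 = 0.10.

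**5. Limit of the illustration.** T0 adjustment also changes the SE, to 0.091 × √(1 − 0.36) = 0.073 at an assumed T0–T1 correlation of 0.6. It would be wrong to take that gain in precision and leave the bias as it was before adjustment. If a stable factor acts equally on T0 and T1, a bias of 0.09 SD falls to 0.09 × (1 − 0.6) = 0.036 SD, and the rejection rate is about 8%. The table is therefore indexed by the bias that remains and keeps the unadjusted SE. It does not predict how much bias will remain.

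**The case against.** The strongest reply is that the causal verbs stand in the introductory and closing text, while the specific objectives and the analysis section are worded with care. The conclusions also do not rest on one coefficient. The study includes ten capabilities interviews per country, a check of consistency across eight countries, and triangulation with three companion studies. The Background also cites three earlier randomised trials. This is fair, and it means the planned analysis is sound as a study of association. None of these elements removes selection into services in this comparison, however, and the Background says that it is this study's comparison that is to do the demonstrating.

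Three stronger readings are tempting and are not supported:

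- **That the study has no check on unmeasured selection.** The article describes none, but a condensed article commonly leaves such a sensitivity analysis to the full protocol or analysis plan, which are not shown. Its absence here is no finding.
- **That the plan will read any significant adjusted coefficient as proof that a feature promotes recovery.** No section states such a rule.
- **That modest selection would be reported as a policy effect.** The article gives no figure from which the residual bias could be derived. The bias might be small, or might run towards the null. Only *could* is supported.

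**Conclusion.** The point holds as a contradiction within the article. A correlational comparison of current service users, with T0 taken after exposure began, is given aims and conclusions that claim effects and mechanisms. An unseen analysis plan could add analyses, but it would not change these published statements.

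Residual selection could be reported as a service effect, with size and direction unknown. The 20% (no clustering) and 12% (design effect 2) at a residual bias of 0.10 SD are illustrations. They rest on an assumed bias, an assumed design effect, a two-sided 5% test and a true effect of zero; only the 240 per group comes from the article. The analysis itself need not change to stand as a study of association. The planned interpretation should.

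**What to change.** 1. In the Background, replace the aim of demonstrating that Housing First reverses homelessness and explaining how it works. In the Discussion and the abstract's Conclusions, replace the reference to features that promote outcomes. Use wording such as *associated with housing and recovery outcomes over 6 months among current service users*, in line with Research Design, Objectives and Statistical Analysis.
2. If causal wording is kept, state the assumptions it needs. For each key contrast, report how strong an unmeasured factor would have to be (group difference times association with the outcome) to bring the confidence limit to zero.

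A pass mark set by the strongest T0 covariate is not advisable as a condition for making recommendations. That covariate may well be the T0 outcome score, which may already reflect the service.

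Cost: wording in three places and more modest published claims. If causal wording is kept, add one short calculation per contrast. No new data are needed.
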